## Abstract

**Background:**

Benefits of physical activity in the management of diabetes are well documented. However, evidence on the effectiveness of interventions integrating physical activity in diabetes care is sparse especially in the countries of the Gulf Cooperation Council. The results from this study will increase our understanding of the use of multi-component interventions aimed at increasing physical activity levels in inactive adults with type 2 diabetes in primary health care in Oman.

**Methods/design:**

The study is a one year 1:1 cluster randomized controlled trial of the MOVEdiabetes programme (intervention) versus usual care in eight primary health care centres in Oman. The MOVEdiabetes programme utilizes face to face physical activity consultations promoting 150 min of moderate to vigorous physical activity per week (≥600MET-mins/week), pedometers to self-monitor step counts and monthly telephone WhatsApp messages for follow up support. Inactive adults with type 2 diabetes and no contraindication to physical activity will be recruited over a two months period, and followed up for 12 months. To demonstrate a 50% between group difference in physical activity levels (MET-mins/week) over 12 months, (at a power of 80%, and significance level of 5%), 128 participants would be required to complete the study (64 in each arm). Based on a drop-out rate of 20%, 154 participants would require to be recruited (77 in each arm). Assuming a recruitment rate of 70%, 220 potential eligible participants would need to be approached. The primary outcome is change in levels of physical activity measured by the Global Physical Activity Questionnaire. In addition, accelerometers will be used in a sub group to objectively assess physical activity. Secondary outcomes include changes in metabolic and cardiovascular biomarkers, change in self-reported health, social support, self-efficacy for physical activity, and perceived acceptability of the program. All intervention delivery and support costs will be monitored.

**Discussion:**

This study will contribute to the evidence on the feasibility, cultural acceptability and efficacy of interventional approaches for increasing physical activity in primary care for persons with type 2 diabetes in Oman.

**Trial registration:**

International Standard Randomised Controlled Trials No: ISRCTN14425284. Registered 12 April 2016.

## Background

The International Diabetes Federation (IDF) estimates that 8.3% of people globally have diabetes (382 million), 90% of which is type 2 diabetes (T2D) and the numbers affected are expected to increase by 55% (to 592 million) by 2035 [1]. In countries of the Middle East and North Africa (MENA) region, the impact of diabetes is a major concern, especially in the Arab Gulf countries which have the highest prevalence of diabetes in the world [2].

Oman, similar to the other high income countries of the Gulf Cooperation Council (GCC) [3], has gone through rapid economic development leading to high energy dense diets and sedentary lifestyles [4]. Diabetes prevalence in Oman increased from 8.3% in 1991 to 11.6% in 2000 and 12.3% in 2008 and recent estimates are in the order of 14.2% [1, 5]. Oman and other GCC countries are facing similar challenges related to management of diabetes and the IDF has estimated that the MENA will have a 96% increase in the number of people with diabetes by 2035 [1, 6].

The evidence around the impact of physical activity (PA) on both the prevention and management of T2D is well documented [7, 8]. To reach the clinical benefits of PA, the World Health Organization (WHO) recommends at least 150 min of moderate-intensity PA OR 75 min of vigorous-intensity PA per week, which equates to an equivalent combination of moderate- and vigorous-intensity PA achieving at least 600 MET-min/week. Meeting physical activity recommendations has been shown to increase insulin sensitivity, lower blood sugar levels, reduce body fat and improve physical condition [9].

Based on the best-available data derived from subjective PA measurement tools (e.g. Global Physical Activity Questionnaire (GPAQ), International Physical Activity Questionnaire (IPAQ-Short) and locally developed questionnaires), the population estimate for adults meeting WHO PA recommendations in Arab countries is around 40% for men and 27% for women [10]. A regional study in Sur (north-east coast of Oman), using GPAQ, showed the highest levels of physical inactivity were in leisure time (55%) and the median sitting time was about two hours/day [11].

While in western countries (USA) it has been reported that over 60% of patients with T2D don’t meet the recommended levels of PA [12], consolidated evidence demonstrating PA levels in populations with T2D in Arabic countries is scarce. In Oman, the national health survey 2008 [5] reported that 15% of adults with T2D were physically active based on international recommendations (150 min per week) while in Lebanon only 10% of adults with T2D were reported to reach the recommended levels of PA versus 23% with inadequate levels [13].

Evidence on the best PA interventions for patients with T2D in primary care worldwide is unclear. Interventions differed by settings (primary care vs community), methods (consultations vs exercise sessions), and duration (short-term vs long-term). PA consultations and exercise sessions linked to theories of behaviour change seem to significantly improve activity levels for patients with T2D [14]. Additionally, technology bound interventions and the use of motivational tools, such as pedometers, have been consistently recommended in interventional studies [15, 16]. Walking interventions have also shown significant positive effects in lowering glycated haemoglobin levels (HbA1c) and improved diabetes health outcomes [17]. However, there is still a gap in the evidence on the best methods, intervention components and intervention intensity that would be most effective in increasing long-term PA in the primary care setting for persons with T2D [14, 18].

Almost all interventions have been carried out in non-Arabic speaking countries hence, evidence for culturally sensitive PA interventions is warranted. Based on these gaps in knowledge, this study aims to explore uncertainties about translating existing evidence from western settings to local clinical settings in Oman whilst taking account of cultural boundaries.

## Methods

### Primary objective

The primary objective is to evaluate the impact of a multi-component intervention (MOVEdiabetes) which aims to achieve 150 min of moderate to vigorous physical activity/week (≥600MET-mins/week) in inactive adults with T2D attending primary health care facilities in Oman.

### Secondary objectives

The secondary objectives of the study are:Estimate the impact of MOVEdiabetes programme on cardio-metabolic risk factors.To evaluate the impact of utilizing a common telephone application, WhatsApp, as an intervention reminder and follow up tool.To examine the acceptability of the intervention (content, delivery and aims) to the participants and project officers (health care providers).To assess the practical issues (including costs) that could challenge or assist programme delivery and roll out.

## Study design/location/recruitment

### Randomisation

The study is a 1 year 1:1 cluster randomized controlled trial of the MOVEdiabetes intervention versus usual care. A cluster randomization design was used to minimize between group contamination by having the two groups (intervention and comparison) from independent health centres. Group allocation will be generated using a random numbers table generated in SPSS v21 by an independent statistician in Oman Ministry of Health. All health centres (8) will be randomised to deliver either the intervention (*n* = 4) or usual care (*n* = 4). Health centres will be informed of their allocation verbally by the project investigator and will receive an envelope containing invitation letter and project materials.

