### Recruitment

To ensure that intervention delivery is institutionalized within routine diabetes care in the selected health centres, three project officers will be recruited at each side (*n* = 24) from existing health care providers (doctors/nurses/dieticians/health educators). Project officers will receive study specific training on the recruitment procedures, screening the participants, recording outcome measurements, and delivering the MOVEdiabetes intervention in intervention health centres (IHC).

All eligible patients attending their routine diabetes clinics in the selected health centers will be informed about the study by the project officers and invited to participate in the study. Interested patients will be screened for physical inactivity using the Scottish Physical Activity Screening Questionnaire (Scot-PASQ) (http://www.paha.org.uk/Resource/scottish-physical-activity-screening-question-scot-pasq﻿).

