## Measures/assessment instruments

Baseline and follow-up data will be collected face to face and from the electronic health information system in the health centre (AlShifa system) (Table 1).

**Table 1 Tab1:** Outcome measures

	Tool	When	
		Intervention	Comparison
Primary outcome			
GPAQ-MET-mins/week	Questionnaire	B, 3 F, 12 F	B, 3 F, 12 F
Accelerometer (activePAL^TM^)	Reporting step count, MET-min/week, and sitting time	B, 3 F, 12 F	B, 3 F, 12 F
Pedometer (YAMAX Digi-walker SW-200)	Reporting step counts	B, 3 F, 12 F	-
Secondary outcomes			
Socio-demographic data	Questionnaire	B	B
Height (m)	Stadiometer	B	B
Body weight (Kg)	Calibrated scales	B, 3 F, 12 F	B, 3 F, 12 F
Waist circumference (cm)	Tape measure	B, 3 F, 12 F	B, 3 F, 12 F
Lipid profile (mmol/l)	Blood test (venous fasted sample)	B, 3 F, 12 F	B, 3 F, 12 F
Blood pressure (mmHg)	Sphygmomanometer	B, 3 F, 12 F	B, 3 F, 12 F
^a^HbA1c (%)	Blood test (fasted sample)	B, 3 F, 12 F	B, 3 F, 12 F
Self-assessed general health	Questionnaire	B, 3 F, 12 F	B, 3 F, 12 F
Self-efficacy for PA	Questionnaire	B, 3 F, 12 F	B, 3 F, 12 F
Social support for exercise	Questionnaire	B, 3 F, 12 F	B, 3 F, 12 F
Cost analysis (description)	Detailed cost description	12 F	-
Exit survey	Questionnaire (participants and project officers)	12 F	-

(B = baseline; 3 F = 3 month follow-up, 12 F = 12 month follow-up)

^a^while blood collection for HbA1c at 12 month is mandatory, it is only done at baseline and 3 month if missing from the electronic health information system or recorded within more than 4 months prior to the measurement visits

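### The same centre officers recruit, coach and record outcomes, apparently knowing the arm, which leaves room for selective enrolment and over-reporting on the GPAQ

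*Protocol article*

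**What the plan says.** All references are to the protocol article.

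- **Allocation and disclosure (Randomisation).** "All health centres (8) will be randomised to deliver either the intervention" or usual care, four centres each. The list is "generated in SPSS v21 by an independent statistician in Oman Ministry of Health". On disclosure: "Health centres will be informed of their allocation verbally by the project investigator and will receive an envelope containing invitation letter and project materials". No time point is given relative to the start of recruitment.
- **Who the officers are and what they do (Recruitment, under Study design).** Three officers per centre are drawn from its existing staff. "Project officers will receive study specific training on the recruitment procedures, screening the participants, recording outcome measurements, and delivering the MOVEdiabetes intervention", the last of these in intervention centres only. They tell patients about the study and invite them.
- **Eligibility and consent (Inclusion criteria; second Recruitment section).** Inactivity is assessed by the project officer, with Scot-PASQ as the screening tool. Officers seek written consent at the baseline visit and log eligible patients who decline. Recruitment lasts 8 weeks.
- **Delivery (Face to face PA consultations; Pedometer).** Officers give three consultations, at weeks 0, 4 and 8. Intervention participants receive a pedometer, with goal-setting by the officer, at the baseline visit.
- **Outcome (Abstract; Measures/assessment instruments, Table 1).** The primary outcome is change in activity on the GPAQ, at baseline, 3 and 12 months. "Baseline and follow-up data will be collected face to face", and also from the electronic record. The person who administers the GPAQ is not named. Accelerometry is done in both arms at the same visits, in a subset.

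**The concern.** Randomising centres protects the comparison only if the patients who then enter do not depend on the arm. An officer who knows the arm may, without intending to, invite or encourage different patients in intervention and usual-care centres.

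The second exposure is measurement. In intervention centres, participants coached towards a weekly activity target may then report their activity, face to face, to the team that coached them. Usual-care participants face no matching pressure. Both exposures bear on the primary outcome, and neither is cured by a larger sample.

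**Working it through.** The document states no figure for this point, so the check is mainly a tracing of who does what, and when.

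**Step 1: is the arm known during recruitment?**
- Disclosure is open, but undated (Randomisation).
- Planned recruits per centre: 154 / 8 = 19.25, entered over 8 weeks.
- Pedometers go only to the intervention arm and are given at the baseline visit, the same visit at which consent is sought.
- Once the first intervention participant in a centre has a pedometer, its officers know the arm while the remaining 18 or so patients are still being screened and consented.
- No step describes recruitment before disclosure.

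Result: knowledge of the arm during recruitment follows from the schedule for intervention centres. For usual-care centres it is likely, since they are told too, but the pedometer argument does not apply to them directly.

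**Step 2: who assesses?**
- Officers are trained to record outcomes in all centres, and to deliver the programme in intervention centres.
- Data are collected face to face, and no independent or masked assessor is mentioned.

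Result: recruitment, coaching and measurement sit with one team of three per centre. The text does not show whether one individual coaches and interviews the same patient.

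**Step 3: do the stated safeguards close the gap?**

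| Safeguard | What it does | What it leaves |
|---|---|---|
| Independent statistician | Protects generation of the list | Later knowledge of the arm |
| All eligible patients invited | Limits choice of whom to approach | Eligibility judgement, encouragement, patient interest |
| Scot-PASQ | Structures the inactivity judgement | It is applied by the same officers |
| Log of decliners | Lets refusals be compared by arm | Describes selection, does not prevent it |
| Accelerometry | Not open to over-reporting | 11 per centre, 8 x 11 = 88, which is 40% of the 220 approached; offered to interested patients until the number is met, so not random and open to the same recruitment |
| Adjustment for noted baseline differences | Handles measured imbalance | Unmeasured motivation, differential reporting |

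The fidelity checks concern consultations and compliance with the intervention protocol, not masking.

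**Step 4: sensitivity of the test (assumed values, not an estimate).** Suppose no true effect, the planned 64 completers per arm, a two-sided 5% test on a normal outcome, and clustering ignored. Let b be a between-arm shift in reported activity, in SD units.

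SE = sqrt(2/64) = 0.177. Rejection probability = 1 - Φ(1.96 - b/SE) + Φ(-1.96 - b/SE).

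| Assumed b | b/SE | Rejection probability |
|---|---|---|
| 0 | 0 | 5% |
| 0.1 | 0.57 | about 9% |
| 0.2 | 1.13 | about 20% |
| 0.3 | 1.70 | about 40% |

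This shows only that the planned comparison cannot tell a modest reporting shift from an effect. The document gives no basis for choosing b.

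**Step 5: timing consequence of delayed disclosure.** If early recruits wait 8 weeks for week 0 and the 3-month visit (about 13 weeks) is still counted from baseline, it falls 13 - 8 = 5 weeks after the start, before the week-8 consultation. Follow-up would have to be counted from week 0.

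**The case against.** The strongest reply is that the text says less than a reader might infer, and that real safeguards exist.

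- *Timing.* A reader might take the Randomisation section to say that officers know the arm before recruiting. It does not; this rests on the baseline-visit pedometer. Nor does the text tie the first consultation to the baseline visit: it is placed at week 0 and, in the accelerometer group, a week after the 7 days of wear. This stands, so the timing is called inferred here.
- *The interviewer.* A reader might conclude that each patient's coach also takes that patient's GPAQ. The text lists training topics for a team and names no GPAQ interviewer, and an article may leave the division of tasks to a fuller protocol. This stands as far as individuals go. The article does fix the combination of roles in one team.
- *Direction.* A reader might infer that both biases must favour the intervention. Over-reporting to coaches plausibly would. Selective enrolment is less clear on a change score: more motivated patients could start higher and have less room to change.
- *Size.* A reader might read the 66 approached patients not expected to enter (220 - 154) as evidence of selection, or express a bias as a share of the planned effect. The 66 is a planning allowance and says nothing about differences between arms. The Sample size section gives a 50% difference without an SD, so no such share can be formed.
- *Safeguards.* Scot-PASQ, the decliner log, two-arm accelerometry and baseline adjustment are real and deserve credit. They mitigate; Step 3 shows what each leaves open.

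**Conclusion.** The concern holds in a limited form. One team per centre recruits, coaches in the intervention arm and is trained to record outcomes. Intervention officers very probably know their arm during the 8-week recruitment, and no separate assessor is named for a self-reported, face-to-face primary outcome. The plan is therefore open to differential recruitment and, in the intervention arm, to over-reporting.

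The size is unknown and the document offers no way to estimate it. The conclusion rests on two inferences: that disclosure precedes or overlaps recruitment, and that officers collect the GPAQ. A passage in the full protocol showing otherwise would remove the corresponding half of the point. The document does not support saying that bias will occur, or that the result would be invalid. The change is worth making because the exposure is on the primary outcome, cannot be repaired reliably in analysis, and is cheap to reduce.

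**What to change.** The parts can be adopted separately.

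1. **Separate assessor.** In each centre, reserve one of the three existing officers to administer the GPAQ and the measurements at 3 and 12 months, with no part in consultations. Cost: two deliverers instead of three, no extra staff. The assessor will still know the arm and participants still self-report, so this reduces bias without eliminating it.
2. **Later disclosure, where feasible.** Complete screening, consent and baseline measures for each centre's 19 to 20 patients before telling the centre its allocation and before delivery training. Count the 3- and 12-month visits from a common week 0 in both arms. Cost: early recruits wait up to about 8 weeks and their baseline values age, including any HbA1c taken from the record, which Table 1 already allows to be up to 4 months old at the visit.
3. **Reporting.** Present accelerometer results by arm beside the GPAQ as a check on reporting bias, noting that the subset is not random. This uses data already planned.

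If part 2 is not adopted, state when centres learn their allocation relative to recruitment. In either case, state who administers the GPAQ.

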### Recruitment

To ensure that intervention delivery is institutionalized within routine diabetes care in the selected health centres, three project officers will be recruited at each side (*n* = 24) from existing health care providers (doctors/nurses/dieticians/health educators). Project officers will receive study specific training on the recruitment procedures, screening the participants, recording outcome measurements, and delivering the MOVEdiabetes intervention in intervention health centres (IHC).

All eligible patients attending their routine diabetes clinics in the selected health centers will be informed about the study by the project officers and invited to participate in the study. Interested patients will be screened for physical inactivity using the Scottish Physical Activity Screening Questionnaire (Scot-PASQ) (http://www.paha.org.uk/Resource/scottish-physical-activity-screening-question-scot-pasq﻿).
**Inclusion criteria**
Adults aged 18 to 60 yearsDiagnosed with type 2 diabetesAttending health centres for at least six months previously for diabetes careAssessed by project officer as having inactive behaviourNo contraindication to physical activityAble to speak and read ArabicWilling and able to provide written informed consent to the study

**Exclusion criteria**
Patients with:Type 1 diabetesA history of myocardial infarction in the previous 6 monthsA serum creatinine >140 mmol/L (from previous recorded readings in the electronic health information system)Diabetic foot ulcers or at high risk of ulcer (severe peripheral neuropathy)Repeated hypoglycaemia or severe hypoglycaemia in previous 12 monthsNo internet access for WhatsAppPhysical activity > 150 min per week

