## Sample size

To demonstrate a 50% between group difference in physical activity levels (MET-mins/week) over 12 months, to be detected at a power of 80%, and significance level of 5%, 128 participants would be required to complete the study (64 in each arm). Based on a drop-out rate of 20%, 154 participants would require to be recruited (77 in each arm). Assuming a recruitment rate of 70%, 220 potential eligible participants would need to be approached.

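### The creatinine exclusion is printed as above 140 mmol/L, a level no patient can reach, so read literally it excludes nobody; the intended value and unit need confirming

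*Protocol article*

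**What the plan says.** The Exclusion criteria section of the protocol article lists a "serum creatinine >140 mmol/L (from previous recorded readings in the electronic health information system" as a ground for exclusion. The value is to be looked up in existing records, and the article describes no new creatinine test at screening.

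Three other places bear on how the line can be read:

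- Table 1 (Measures/assessment instruments) has no creatinine row. The only blood measure it gives in this unit is "Lipid profile (mmol/l"), so no second creatinine unit is available for comparison.
- The entry requirements include "no contraindication to physical activity", in the abstract and again under Inclusion criteria. Kidney function is not named.
- The Recruitment subsection under Study design says that screening is done by project officers, three at each of eight centres (24 in all). They are drawn from doctors, nurses, dieticians and health educators and trained for the study.

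**The concern.** The line gives a number and a unit that cannot belong together. Serum creatinine in patients is a fraction of 1 mmol/L, or at most a few mmol/L in extreme kidney failure, so a cut-off of 140 in that unit lies outside anything a laboratory would report. A screening form or database query that respects the unit would never trigger the exclusion.

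This is the only numeric laboratory threshold among the entry criteria. The article does not label it a safety rule, but that is a reasonable inference: it stands in a list with recent myocardial infarction, foot ulcer and severe hypoglycaemia, and the programme aims for 150 minutes of moderate to vigorous activity a week. At stake is whether an eligibility rule that the sponsor chose to include can operate as written.

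This is a stated figure that is wrong, not a detail left out of a condensed article. A statistical analysis plan would not normally correct an eligibility threshold.

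**Working it through.** **Inputs**

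- Threshold: above 140 mmol/L (Exclusion criteria).
- Molar mass of creatinine: 113.12 g/mol, which is 113.12 mg/mmol. This is a chemical constant, not in the article. It is needed only for the mg/dL figures.
- Range of recorded creatinine: 60 to 2,000 µmol/L, from normal to extreme kidney failure. This is an assumption, not in the article. A deliberately implausible 5,000 µmol/L is added as a stress test.

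The article derives no figure here, so there is nothing to reproduce. Its sample size, power and significance level play no part.

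**Step 1: convert the printed threshold**

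- 140 mmol/L × 1,000 = 140,000 µmol/L
- 140 mmol/L × 113.12 mg/mmol = 15,836.8 mg/L, about 15.8 g/L
- 15,836.8 mg/L ÷ 10 = 1,583.7 mg/dL, about 1,580 mg/dL

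**Step 2: compare it with the assumed range**

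Ratio = 140 mmol/L ÷ (recorded value in mmol/L).

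| Recorded value | In mmol/L | Threshold ÷ value |
|---|---|---|
| 60 µmol/L | 0.06 | 2,333 |
| 100 µmol/L | 0.10 | 1,400 |
| 500 µmol/L | 0.50 | 280 |
| 1,000 µmol/L | 1.0 | 140 |
| 2,000 µmol/L | 2.0 | 70 |
| 5,000 µmol/L | 5.0 | 28 |

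No value in the table comes near the threshold. The conclusion is the same wherever one stands in the assumed range.

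**Step 3: what reading the bare number would do**

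A screener might ignore the unit and compare 140 with whatever figure the record shows. The result depends on the laboratory's unit:

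- Records in µmol/L: 140 µmol/L = 0.140 mmol/L, and 0.140 × 113.12 ÷ 10 = 1.58 mg/dL. This is 1,000 times lower than the printed threshold and falls inside the assumed range, so the exclusion would operate.
- Records in mg/dL: 140 mg/dL = 1,400 mg/L, and 1,400 ÷ 113.12 = 12.38 mmol/L, about 12,400 µmol/L. This is still about 6 times the top of the assumed range (12,376 ÷ 2,000 = 6.2), so nobody would be excluded.

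These conversions show scale only and are not proposals for the threshold. The article does not state the unit in which the health information system reports creatinine.

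**Step 4: look for a passage that repairs the line**

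Creatinine is mentioned once in the article. Table 1 does not list it, and no other criterion names kidney function. The requirement of no contraindication to activity leaves room for judgement but supplies neither value nor unit.

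**The case against.** The strongest reply is that this is one wrong prefix. Screeners are trained health care staff reading stored results from a local records system, and they would most naturally compare 140 with the number on the screen. If that system reports in µmol/L, the exclusion would work in practice. This stands, and it limits the point to the written rule. It does not remove the point, because the article never gives the system's unit, and step 3 shows that the bare-number reading does not work in every unit.

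Second, the text at hand was read from PDF by a program, and a µ could have become an m. This cannot be excluded, although other special characters, such as ≥ and the table arrows, came through intact. A look at the typeset article settles it; if it prints µmol/L, the point falls.

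Third, the requirement of no contraindication to physical activity is a partial backstop. A project officer could use it to keep out a patient whose kidney disease rules out activity. That is fair, but it relies on individual judgement and does not restore the threshold.

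A reader might also infer more than the documents support:

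- **Imbalance between arms, because centres are the randomised units.** Nothing shows that centres read the line differently. One records system (AlShifa) is named and screening training is described, which makes a common reading more likely.
- **A number affected among the 220 to be approached.** Those are described as potentially eligible people, and the article gives no creatinine distribution. The number affected is unknown and may be zero.
- **A fault in setting no age limit on the stored creatinine, when Table 1's footnote sets 4 months for HbA1c.** HbA1c is a trial outcome that needs a timely value, while creatinine is a screening check. The two need not match, and a journal article may leave a look-back window to the full protocol.

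**Conclusion.** The criterion is wrong as printed. Its threshold is 140,000 µmol/L (about 1,580 mg/dL), 70 times the top of the assumed range and 28 times an implausible 5,000 µmol/L. Read literally, it excludes 0% of patients. That result rests on the assumed range, but no plausible change to the range alters it.

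The likeliest cause is a unit misprint, by a factor of 1,000 if µmol/L was meant. That is an assumption for the sponsor to confirm, since nothing in the article establishes the intended unit.

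The finding does not show that any ineligible patient was enrolled or that the arms differ. It has no bearing on the primary outcome, the sample size or the analysis. It still deserves correction, because it is an operative eligibility threshold and not background text, and the correction is cheap.

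**What to change.** 1. Check the typeset article and the full protocol to see whether the unit is printed the same way.
2. Have the sponsor confirm the intended value and unit against the unit in which the health information system reports creatinine. No threshold is proposed here.
3. Correct the criterion in the protocol and in the screening materials.
4. Notify all 24 project officers of the corrected line.
5. Re-check the stored readings of anyone already screened against the confirmed criterion, and document the result.

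The cost is a one-line correction, one notice to staff and a look-up of existing records. No new blood test is needed for this correction. If the line has been applied literally, a few patients may prove to have been ineligible; if staff already used the intended value and unit, nothing changes beyond the text.
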